## Abstract

**Introduction:**

*Hibiscus syriacus* L. flower (HSF) is a food ingredient commonly used for tea, and previous animal studies have reported its sleep-promoting effect. This study aims to test the potential of HSF extract as functional food that improves sleep in humans.

**Methods and analysis:**

Eighty participants with sleep disturbances who meet the inclusion/exclusion criteria will be enrolled in this study. Since the effect of HSF extract on sleep is considered to be that of a functional food rather than a medicine, participants with severe insomnia will be excluded from the study. The enrolled participants will be randomly assigned to the HSF extract or placebo groups in a 1:1 ratio. The HSF extract and placebo capsules will look identical, and participants, investigators, and outcome assessors will be blinded to the allocation. Four capsules of HSF extract or placebo will be orally administered 30–60 min before bedtime for 4 weeks. The primary outcome of this study will be the change in the Pittsburgh Sleep Quality Index (PSQI) global score from the baseline after 4 weeks. The subjective and objective changes in the participants’ sleep will be evaluated using the Insomnia Severity Index (ISI), Epworth Sleep Scale (ESS), sleep diary, and polysomnography (PSG). The occurrence of adverse events will be closely monitored.

**Discussion:**

The results of this trial will provide data on the efficacy and safety of HSF extract in enhancing sleep quality. Based on the results, the potential of HSF extract as a functional food that improves sleep in humans will be evaluated, and the findings of the trial will be submitted to the Korean Ministry of Food and Drug Safety for consideration as a new functional ingredient that may help to improve sleep quality.

**Clinical trial registration:**

: Clinical Research Information Service: KCT0007314; Registered 19 May 2022, https://cris.nih.go.kr/cris/search/detailSearch.do/21497.

## 1. Introduction

Sleep is essential factor for maintaining physical and psychological well-being (1). Poor sleep has been found to be associated with reduced productivity and impaired work performance (2, 3), and insufficient sleep has been linked to an increased risk of cognitive decline (4). Despite the importance of sleep, dissatisfaction with sleep quantity or quality is prevalent among the general population, with up to 41.7% of individuals reporting insufficient sleep and 30–48% reporting difficulties with sleep initiation or maintenance (5, 6). Although medication may be effective for treating severe insomnia, there is still an unmet need for safe and accessible sleep aids for individuals with suboptimal sleep quality (7). One potential solution is the use of functional foods, which contain bioactive compounds that offer health-promoting properties (7, 8).

Several functional foods have been suggested as potential aids for improving sleep quality (7, 9, 10). For example, valerian, one of the botanical dietary supplements sold in the United States as sleep aids (11, 12), and chamomile, which is commonly consumed as a tea, have been reported to have beneficial effects on sleep quality (13, 14). In Korea, five functional food ingredients have been granted health claims for “may help to improve sleep quality” (15), including Ecklonia cava ethanol extract (16, 17), milk protein hydrolysate (Lactium) (18), rice bran ethanol extract (19), fermented L-glutamate GABA powder (20), and ashwagandha extract (21). The health functionality of these ingredients was established based on their sleep-promoting effects demonstrated in human and animal studies.

*Hibiscus syriacus* L. flower (HSF) is a food ingredient (22) that has been widely used to make flower tea. The root of *Hibiscus syriacus* L. is used as a medicine, and its effects on wound healing (23), depression-like behaviors, and neuroprotection (24) have been reported. Meanwhile, HSF has shown a sleep-promoting effect in three sleep-related animal models (25). The HSF extract and its active component (saponarin) increased the rapid-eye-movement sleep time in an electric foot shock-induced sleep disturbance model, restored sleep duration in a restraint-induced sleep disturbance model, and increased sleep maintenance time in a pentobarbital-induced sleep model (25). Based on the results of previous animal studies, the effect of HSF extract on sleep improvement needs be tested in humans.

The objective of this randomized, double-blind, placebo-controlled, parallel-group clinical trial is to evaluate the efficacy and safety of HSF extract on sleep improvement in adults with sleep discomfort and to compare them with that of placebo. Eighty participants will be randomly allocated to the HSF extract or placebo groups in a 1:1 ratio. The superiority of the HSF extract over placebo will be tested.

## 2. Methods and analysis

### 2.1. Study setting

This clinical trial will be conducted in two academic university hospitals in Korea, one in Seoul and the other in Daegu.

### 2.2. Eligibility criteria

This trial targets those individuals with subjective sleep complaints who are in their sub-health status, not the disease. Patients with severe insomnia will be excluded from the study.

#### 2.2.1. Inclusion criteria

Participants aged between 19 and 65, with a Pittsburgh Sleep Quality Index (PSQI) global score of 5 or higher, Insomnia Severity Index (ISI) score between 8 and 21, and who agree to participate and sign the informed consent form will be included.

#### 2.2.2. Exclusion criteria

The exclusion criteria are as follows: participants with severe diseases in cardiovascular system, immune system, respiratory system, gastrointestinal/hepatic and biliary system, kidney and urinary system, nervous system, musculoskeletal system, infectious disease, or malignant tumor; with diseases or symptoms that could affect sleep, such as nocturia; with mental diseases, including alcohol-use disorder, major depressive disorders, generalized anxiety disorders, post-traumatic stress disorders, and obsessive–compulsive disorder; with a past history of or currently suffering from schizophrenia or bipolar disorder; with cognitive decline; with sleep disorders including insomnia, narcolepsy, obstructive sleep apnea, and restless legs syndrome; with irregular sleep patterns due to night-shifts; current smokers, heavy caffeine drinkers, or excessive alcohol drinkers; those taking medications or dietary supplements that could affect sleep within 4 weeks. To exclude participants with clinical depression and anxiety, the Patient Health Questionnaire-9 (PHQ-9) (cut-off: 10 points) (26) and Generalized Anxiety Disorder-7 (GAD-7) (cut-off: 5 points) (27) will be used for the screening test. To exclude participants with a high risk of sleep apnea, STOP-Bang Sleep Apnea Questionnaire (cut-off: 5 points) (28) will be used for the screening test. The complete exclusion criteria with detailed information can be found in the clinical trial registration.^1^

### 2.3. Intervention

Four capsules containing HSF extract or placebo will be orally administered 30–60 min before bedtime for 4 weeks. The investigational products are manufactured as brown-colored hard capsules. One HSF extract capsule (500 mg) includes 250 mg of HSF extract as an active ingredient. The participants in the HSF extract group will take 1,000 mg of HSF extract per day. Placebo capsules have an appearance identical to that of the HSF extract capsules and contain maltodextrin and no active ingredients.

Discontinuing or modifying the allocated intervention is not planned, except in case of the participant’s refusal. To monitor adherence, the pharmacists will check for compliance at every visit after prescribing the HSF extract or placebo capsules, and all the remaining capsules will be returned to the clinical pharmacies. During the study period, concomitant care or interventions will be prohibited, except in exceptional cases. Only those medications, dietary supplements, and other treatments initiated before participation in this study that will not affect the results of this study can be permitted. Furthermore, even during the course of the study, if the administration of a medicine is required for the transient treatment of other diseases and the medication is considered to not affect the result, it can be permitted.

### 2.4. Outcomes

#### 2.4.1. Primary outcome

The primary outcome of this study is the change from the baseline of the PSQI (29, 30) global score after 4 weeks of administration. The PSQI is a representative self-rated questionnaire that assesses sleep quality and disturbances for over a month. A higher PSQI global score indicates poor sleep quality.

#### 2.4.2. Secondary outcome

The secondary outcomes include the ISI (31, 32) and Epworth Sleepiness Scale (ESS) (33, 34) to assess the severity of insomnia and daytime sleepiness, respectively. The ISI and ESS will be measured at baseline, 2 weeks (during treatment), and 4 weeks (post-treatment). Polysomnography (PSG) will be performed at baseline and at 4 weeks (post-treatment) for one night, and the total sleep time (TST), sleep efficiency (SE), sleep onset latency (SOL), and wake-up after sleep onset (WASO) will be assessed. The participants will be instructed to keep a sleep diary during the study period. The TST, SE, SOL, and WASO for 7 days will be extracted from the sleep diary at baseline, 2 weeks, and 4 weeks. Blood biomarkers of cortisol, C-reactive protein, and adiponectin will be measured at baseline and at 4 weeks to assess the stress levels and inflammatory markers. The participant timeline is shown in Figure 1.

**Figure 1 fig1:**
[figure not shown]
The schedule of enrolment, intervention, assessment, and visits for participants. ^1^The day after the polysomnography. PHQ-9, Patient Health Questionnaire-9; GAD-7, Generalized Anxiety Disorder-7; PSQI, Pittsburgh Sleep Quality Index; ISI, Insomnia Severity Index; ESS, Epworth Sleepiness Scale; PSG, Polysomnography.

### 2.5. Sample size

The primary objective of this clinical trial is to evaluate the superiority of the PSQI global score improvement in the HSF extract group compared to that in the placebo group. To estimate the mean difference of the PSQI global score between both groups and the pooled standard deviation, the results of a previous randomized trial (35) will be used to assess the PSQI global score. In the earlier trial, the mean difference of change from baseline between the two groups was −3.95 (−3.96 in the treatment group and − 0.01 in the placebo group). The standard deviation of the change from baseline was not presented, and the largest value of the standard deviation of the PSQI global score was 3.4. To calculate the sample size for this study, the mean difference and pooled standard deviation were estimated as −2.50 and 3.4, respectively. With a 5% level of significance, 80% power of the test, and 25% dropout rate, the required sample size for each group was calculated as 40.

### 2.6. Recruitment

Adults with sleep disturbance are being recruited based on the outpatients of two university hospitals in Korea. The clinical sites are located in two metropolitan cities in Korea: Seoul and Daegu. A poster regarding this clinical trial is being posted on the bulletin board and internet homepage of both the hospitals. To enhance the recruitment rate, local advertisements can also be conducted at the bus stops near the hospitals.

### 2.7. Randomization and allocation concealment

An independent statistician generated the random allocation sequence using the randomization program of the SAS^®^ system (version 9.4). The allocation ratio for the HSF extract and placebo was 1:1, and the block size was concealed from the other investigators. An investigator affiliated with Dongkook Pharmaceutical, who is in charge of the management of the random allocation sequence and packaging of investigational products, packed the HSF extract capsules and placebo capsules according to the allocated random number. The investigational products were packed identically, and each random number was labeled in the package. The investigators in charge of the enrollment of participants were blinded for the allocation sequence and sequentially assigned the random numbers to the enrolled participants.

### 2.8. Blinding

The participants of the trial, investigators, and outcome assessors will be blinded to the group assignment. Placebo and HSF extract capsules have been developed to have an identical appearance. Concealed envelopes containing information on the group assignment of each random number are being managed by the principal investigators at the two sites. These concealed envelopes will not be disclosed until the completion of this clinical trial unless unblinding is inevitable owing to serious adverse drug reactions or important clinical issues. In such cases, the investigators should immediately contact the sponsors and provide detailed information about the situation. The sponsors and investigator, only after thorough examination, will decide whether or not code breaking for the participant is necessary. The process and reason for the unblinding will be recorded, and the unblinded participants will be dropped from the trial.

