### 2.12. Data monitoring and auditing

The estimated risk of the trial is low because the investigational product of this trial is a food. A data monitoring committee is not required and an interim analysis is not planned.

A contract research organization hired by sponsors will monitor the clinical trial to verify the process of informed consent acquisition, conduct the trial in compliance with the approved protocol, and obtain accurate and complete trial data. The initial monitoring visits for each site are scheduled within 7 days of the enrollment of the first participant. Routine monitoring will also be conducted 10–11 times at each site.

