### 2.13. Harms

Adverse events will be carefully assessed through non-directive questioning during the trial period. The symptoms and signs of adverse events in participants will be collected at every visit, and their severity and causality will be assessed. Blood and urine tests will be conducted before and after the intervention, and clinically significant abnormal results will be assessed. Owing to the characteristics of the investigational product as a health functional food, product-related severe adverse events are not expected, and mild dyspepsia may occur.

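### One code-break rule covers urgent and non-urgent cases, and gives the site investigator no route to open an envelope in an emergency before the sponsors agree

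*Protocol article*

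**What the plan says.** The whole procedure is in section 2.8 of the protocol article.

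- **Custody.** "Concealed envelopes containing information on the group assignment of each random number are being managed by the principal investigators at the two sites".
- **Trigger.** The envelopes stay closed until the trial is complete, "unless unblinding is inevitable owing to serious adverse drug reactions or important clinical issues".
- **First step.** When that happens, "the investigators should immediately contact the sponsors and provide detailed information about the situation".
- **Decision.** "The sponsors and investigator, only after thorough examination, will decide whether or not code breaking for the participant is necessary".
- **Record and consequence.** "The process and reason for the unblinding will be recorded, and the unblinded participants will be dropped from the trial".

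Two other sections bear on how often this would matter. Section 2.12 states: "The estimated risk of the trial is low because the investigational product of this trial is a food". Section 2.13 adds that "product-related severe adverse events are not expected" and names mild dyspepsia as a possible effect. Neither section gives another route to the allocation. Section 4.3 names two sponsoring institutes.

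**The concern.** Single-participant envelopes at the site let the treating side learn one allocation quickly without exposing the rest of the sequence. The article then makes opening them depend on a joint decision with parties who are not at the site, to be taken only once a thorough examination has been made. At least part of the trigger, a serious adverse drug reaction, can be an urgent event, and nothing in the procedure is adapted to urgency.

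What is at stake is participant safety. If knowing the allocation matters for someone's care, the written rule does not let the investigator at that person's site obtain it on his or her own judgement. An investigator who opened the envelope first would be departing from the protocol.

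**Working it through.** No arithmetic applies. The rule contains no figure and does not depend on the sample size, power or analysis method. The check is to read the steps of section 2.8 in order and ask what an investigator who follows them exactly may do.

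1. **Is the envelope within reach?** Yes. It is held by the principal investigator at the site.
2. **May it be opened before trial completion?** Only if unblinding is *inevitable* for one of two reasons: a serious adverse drug reaction or an important clinical issue. The first can be urgent. The second may or may not be.
3. **What must come first?** Contact with the sponsors, with detailed information. The word *immediately* governs this contact. It does not govern the decision or the opening of the envelope.
4. **Who decides?** The sponsors and the investigator together. The decision comes *only after* a thorough examination, so the article itself makes that examination a precondition.
5. **Can the answer be no?** Yes. The decision is *whether or not* code breaking is necessary.
6. **Is there an exception for urgent care?** None in section 2.8. Sections 2.12 and 2.13 describe the level of risk and the collection of adverse events and add no unblinding route.

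Two results follow.

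- **The steps do not fit together.** Step 2 admits only cases where unblinding is already inevitable. Steps 4 and 5 then ask whether it is necessary. If it is inevitable, the later decision has nothing left to settle. If the question is still open, the trigger is worded too strongly. The two sentences need reconciling on their own terms.
- **No urgent route exists.** Steps 3 to 6 together mean that an investigator who keeps to the text cannot open the envelope before the sponsors have joined in the decision. Delay and refusal are both outcomes that the wording permits. It does not say that either will occur.

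On frequency, the documents give no expected number of code breaks. The rule covers all 80 planned participants, and the stated expectations in sections 2.12 and 2.13 point to few cases.

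**The case against.** The strongest reply has four parts.

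- **The trigger is not purely urgent.** Important clinical issues can include matters where joint review is sensible. This stands. The fault is that one rule serves both kinds of case, and joint review as such is not the fault.
- **The article condenses a fuller protocol.** Time limits, contact arrangements and code-break forms commonly sit in that document, and their absence here is no fault. This also stands. It does not dispose of the point, because the article does more than stay silent: it states a restrictive rule without exception, and an investigator-alone route in the fuller document would contradict that sentence.
- **The article asks for immediate contact, makes the investigator a co-decider and states no sponsor veto.** That is fair as far as it goes. But a joint decision with no rule for disagreement still leaves the investigator unable to act alone.
- **The risk is low, and nothing in the article shows that knowing extract from placebo would change emergency care.** This limits the practical size. It does not remove the need for an emergency provision that works in the unexpected case.

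A reader might infer more than the documents support:

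- *Events would cluster out of hours because the capsules are taken before bedtime.* The article gives no onset times and says nothing about how reachable the sponsors are.
- *The delay is unlimited.* The article is silent on timing, and silence is not a rule that permits any delay.
- *The procedure biases the analysis.* Section 2.7 does describe "An investigator affiliated with Dongkook Pharmaceutical, who is in charge of the management of the random allocation sequence", and section 4.3 provides for a blind review of the analysis set. But no section says that this person takes part in code-break decisions or in that review, and discussing clinical details before a code break does not reveal the allocation.

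**Conclusion.** The point holds in a limited form. Section 2.8 fixes a single code-break procedure for urgent and non-urgent cases, and under it the site investigator has no route to open an envelope in an emergency before the sponsors agree. Access to the allocation can therefore be delayed or declined, even though the envelope is at the site and the trigger presupposes that unblinding cannot be avoided.

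The consequence concerns participant safety. No effect on the primary comparison, the sample size or the blind review is shown. Few participants are likely to be affected, given the article's own statements about risk. The change is still worth making, because the rule applies to everyone randomized and the correction is cheap.

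The conclusion rests on two assumptions: that the article reports the operative rule faithfully, and that *only after* means what it says. If the full protocol already contains an emergency route, the article misstates it and the two texts should be brought into line.

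**What to change.** Reword section 2.8, and the matching text of the full protocol, to separate two cases.

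- **Urgent.** When the allocation is urgently needed for a participant's care, the site investigator may open that single participant's envelope without prior agreement from the sponsors. The investigator then promptly notifies the sponsors and records the date, the reason and who opened it. The process and reason are already to be recorded; the date and the opener should be named explicitly.
- **Non-urgent.** Keep the joint decision of the sponsors and investigator after examination of the case.

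In the same edit, reconcile the trigger with the decision step, so that the text no longer requires unblinding to be inevitable and then asks whether it is necessary.

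The cost is a few sentences, a matching line on the code-break record, and approval by both institutional review boards, which section 4.1 requires for any amendment. The downside is a slightly higher chance of an unnecessary code break. It is limited because each opening exposes one participant only and must be justified in writing.

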### 2.11. Statistical methods

#### 2.11.1. Definition of the population to be analyzed

The main population to be analyzed for evaluating efficacy is the Per Protocol (PP) set, and Full Analysis (FA) set will be used supplementary. The PP set will include participants who complete the trial without major deviations from the planned protocol. The FA set will include an additional population for evaluating the efficacy and will include participants who are randomized into groups and who complete more than one assessment after the administration of the investigational products. The main analysis population for evaluating safety will be the safety set, which includes participants administered the investigational products more than once. In the primary and secondary outcomes, there will be no missing data in the PP set, and missing data in the FA set will be imputed using the last observation carried forward method.

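### Dropping every unblinded participant from the trial merges loss of the blind with the end of follow-up, and so loses week-4 outcomes and later safety data after a clinical event

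*Protocol article*

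**What the plan says.** Section 2.8 (Blinding) keeps the allocation envelopes closed until the trial ends, "unless unblinding is inevitable owing to serious adverse drug reactions or important clinical issues". The sponsors and the investigator decide on each code break after examining the case. The section then sets the consequence: "The process and reason for the unblinding will be recorded, and the unblinded participants will be dropped from the trial". The drop is from the trial; the sentence does not limit it to the product or to one analysis.

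Section 2.11.1 sets the analysis populations.

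- Efficacy: "The main population to be analyzed for evaluating efficacy is the Per Protocol (PP) set, and Full Analysis (FA) set will be used supplementary".
- PP set: "The PP set will include participants who complete the trial without major deviations from the planned protocol".
- FA set: "participants who are randomized into groups and who complete more than one assessment after the administration of the investigational products", and "missing data in the FA set will be imputed using the last observation carried forward method".
- Safety: "the safety set, which includes participants administered the investigational products more than once".

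Section 2.13 (Harms) ties safety data to attendance: "The symptoms and signs of adverse events in participants will be collected at every visit, and their severity and causality will be assessed". It also places blood and urine tests before and after the intervention, and expects no severe events related to the product. Section 2.3 names only the participant's refusal as an exception to its statement that discontinuation of the allocated intervention is not planned.

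**The concern.** Three things are separate: someone learns the allocation, the participant stops the product, and the participant leaves follow-up. Section 2.8 makes the third follow from the first. A broken code is a reason to record who knows the allocation and when. It does not by itself justify ending data collection.

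Both triggers are clinical events after randomisation, and one is a suspected reaction to the product. If such events are more frequent in one arm, participants are lost unequally and not at random. Two things are at stake: the fairness of the week-4 PSQI comparison, and the completeness of safety follow-up after events of particular interest. The article describes this as the first human study of the extract for sleep (section 3), and its efficacy and safety results are to go to the Korean regulator (section 4.4).

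**Working it through.** **1. What a dropped participant contributes, section by section**

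| Data or analysis | Result for a participant dropped before week 4 |
|---|---|
| Triggering event and earlier safety data | Kept in the safety set if the product was taken more than once (2.11.1) |
| Later scheduled adverse-event visits | Not obtained (2.8 with 2.13) |
| Post-intervention blood and urine tests | Not obtained as scheduled (2.8 with 2.13) |
| Week-4 PSQI, polysomnography and other week-4 outcomes | Not obtained (2.8 with 2.4) |
| PP set (main efficacy analysis) | Excluded, because the set requires completion (2.11.1) |
| FA set (supplementary) | Only with more than one assessment after administration; the week-4 value is then carried forward (2.11.1) |

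Entry to the FA set is uncertain for such a participant. Before week 4, section 2.4.2 gives one assessment time after baseline, week 2. If assessments are counted as visits, a participant dropped before week 4 fails the criterion. If they are counted as instruments, the week-2 ISI and ESS could satisfy it. The text names no week-2 PSQI, and the schedule figure is not available here. If there is none, carrying forward means carrying the baseline, which is a change of zero.

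**2. The plan's own figure**

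Inputs from section 2.5: difference 2.50, SD 3.4, 5% level (two-sided assumed, as sidedness is not stated), 80% power, 25% dropout, 40 per group.

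- n = 2 × (1.960 + 0.842)² × 3.4² / 2.50² = 29.03, rounded up to 30 per group.
- 30 / (1 − 0.25) = 40 per group. The stated figure reproduces.

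Normal-approximation power is 0.813 at 30 evaluable per group, 0.800 at 29 and 0.786 at 28. A few code breaks hardly affect power. The dropout allowance protects power only; it does not remove bias from selective loss.

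**3. Illustrative size of the bias**

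The documents give no code-break rate and no PSQI course for such participants, so these inputs are assumptions. Suppose k of N participants in an arm are removed, and their mean change would have been D points worse than that of the rest. The arm mean then shifts by (k/N) × D.

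- Worked case: N = 40, k = 2, both with no change, the other 38 at −2.5. The mean of all 40 is (2 × 0 + 38 × (−2.5)) / 40 = −2.375. After removal it is −2.5. The shift is 0.125 points, which is 0.125 / 2.50 = 5% of the planned difference.
- Range for k = 1 to 3 and D = 2.5 to 5:

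| N in the arm | Smallest shift | Largest shift | Share of 2.50 |
|---|---|---|---|
| 40 | 1/40 × 2.5 = 0.06 | 3/40 × 5 = 0.38 | 2.5% to 15% |
| 30 | 1/30 × 2.5 = 0.08 | 3/30 × 5 = 0.50 | 3% to 20% |

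For scale, the standard error of the difference at 30 per arm is 3.4 × √(2/30) = 0.88, so the worked case is 0.125 / 0.88 = 0.14 standard errors.

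**4. Sections 2.3 and 2.8 side by side**

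Section 2.3 gives refusal as the only exception for discontinuing the allocated intervention. Section 2.8 adds a second route out that the participant does not choose. The two sections must be reconciled.

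**The case against.** The strongest reply is that the analysis sets already do much of the work. Section 2.8 does not say that collected data are deleted. The safety set keeps the triggering event, and the FA set can keep the participant with a carried-forward value. If there is no interim PSQI, that value is zero change, exactly what the worked case assumes, so for an FA participant the illustrated shift disappears. This stands, and it limits the loss to data that would have been collected later. It does not help the PP set, which is the main efficacy analysis, and a carried-forward value is not an observed one.

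A reader might infer that the rule removes participants because they did badly on efficacy, and so favours the arm with more reactions. The documents do not support that. The triggers are clinical events and not PSQI scores, and nothing links them to poor PSQI change. A reader might also infer that code breaks will be mainly for serious reactions. The text lists two triggers and does not rank them.

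It can also be said that follow-up of an ongoing adverse event after withdrawal is often left to the full protocol, which is not shown. That stands as a caution on the safety part. The article nonetheless states a positive rule of dropping from the trial, and nothing in it continues assessments afterwards.

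Finally, few cases are likely. Code breaking is reserved for unavoidable situations, treatment lasts 4 weeks, and section 2.13 expects no severe product-related events. This stands, and it makes the point a cheap improvement. It does not make the trial invalid.

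**Conclusion.** The concern holds in a limited form. As written, section 2.8 ends scheduled follow-up for any participant whose code is broken, after a clinical event that may differ by arm. The triggering event and earlier safety data are kept. The week-4 outcomes, later scheduled adverse-event visits and post-intervention laboratory tests are lost, and the participant is excluded from the main efficacy set. The rule can therefore bias the comparison and shorten safety follow-up.

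The likely effect is small and may be nil. Under the assumptions shown, two such participants in an arm of 40 move its mean by 0.125 points, and the wider assumed range is 0.06 to 0.50. These figures rest on an assumed number of code breaks and an assumed worse PSQI course, so they show scale and not direction. The safety conclusion rests on the literal meaning of the clause and would weaken if the full protocol continues adverse-event follow-up after a drop.

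**What to change.** - **Section 2.8:** replace the final clause. Unblinding is recorded and flagged, with date, reason and who learned the allocation. Scheduled outcome and adverse-event data continue to be collected, with the participant's consent and whether or not the product is still taken. The participant is analysed in the randomised arm in the FA and safety sets. A sensitivity analysis excludes PSQI scores obtained after unblinding.
- **Section 2.11.1:** state that unblinding alone does not remove a participant from the FA set. Acknowledge that the change does not cure the PP-first main analysis, because an unblinded participant may still be excluded from the PP set as a major deviation.
- **Sections 2.3 and 2.8:** reconcile the stated grounds for discontinuation. Which rule should apply is for the sponsor and investigators to decide.

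The cost is a replaced clause in 2.8, a sentence or two in 2.11.1 and the reconciliation with 2.3. The downside is a few self-reported scores collected when the participant may know the allocation, which the sensitivity analysis covers.
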